##### 10.4.2. Administration compliance

Compliance is ensured by administering all investigational drugs under the supervision of the investigator or the person who has been delegated by the investigator at the clinical study institution. Non-compliant subjects (e.g, those who are not present for a scheduled visit or who break the restrictions) may be excluded from the clinical study and will be recorded in the eCRF accordingly. The investigator administers the investigational drug to the subject and confirms the intake through oral examination.

##### 10.4.3. Concomitant Medications

Subjects are prohibited from taking concomitant medications from the time of screening to the end of the study. However, if concomitant medication is used for medical need, the concomitant medication may be administered under the judgment of the investigator (principal investigator or doctor in charge). If it is expected that the drug taken by the subject arbitrarily may affect the safety, tolerability, and pharmacokinetic evaluation, which is the object of this clinical study, the subject may be withdrawn at the discretion of the investigator. For all administered concomitant medications, the drug name (ingredient name, brand name in case of combination), route of administration, daily dose, duration of administration (start and end), and reason for taking are recorded in the source document and eCRF.

#### 10.4.4. Prohibited Concomitant Medications and Foods

- All prescription drugs and herbal medicines are prohibited from 2 weeks prior to first investigational drug administration to the end of clinical study.
- Antidepressants (SSRI, SNRI, tricyclic, tetracyclic, triazolopyridine) are prohibited from 2 weeks before administration of the investigational drug to 2 weeks after administration of the last investigational drug, and Fluoxetine is prohibited from 5 weeks before the administration of the investigational drug to 2 weeks after the last administration of the investigational drug.
- Dietary supplements or vitamin supplements including all over the counter drugs (OTCs) or liver function supplements are prohibited from 1 week prior to first investigational drug administration to the end of clinical study.
- Those who continuously drink alcohol (more than 21 units/week, 1 unit = 10 g of pure alcohol) cannot participate in the clinical study, and alcohol must be abstained from 3 days before the first administration to the end of the clinical study.
- Grapefruit, grapefruit juice, foods containing grapefruit, and caffeine/foods containing caffeine (coffee, tea (black tea, green tea, etc.), carbonated drinks, coffee-flavored milk, nutritional tonics, etc.) are prohibited during the period from 3 days before the first administration to the end of the clinical study.
- Foods rich in tyramine (cheese, processed meat, pickled vegetables, soybean paste, citrus fruits, etc.) are prohibited during the period from 1 day before the first administration to discharge.

#### 10.5. Dose Escalation to the Next Dose Level

When safety data up to the the last pharmacokinetic sampling day of the all subjects for each dose group are available, the next dose level can proceed if it is determined that safety and tolerability have been adequately demonstrated through the review of the internal safety review committee (SRC) composed of the Investigators and the Sponsor. The elderly dose group(120 mg) of the multiple dose study proceeds after the maximum tolerated dose (MTD) group or the 480 mg dose group is completed. When proceeding from a single dose study to a multiple dose study, and when determining the administration dose in the elderly dose group within the multiple dose study, the appropriate administration dose is determined after review by the Safety Review Committee (SRC) including independent experts. The SRC is made up of the investigators, the sponsor, and cardiovascular or neurological experts.

When determining whether safety and tolerability have been adequately demonstrated, the Principal Investigator remains blind to the treatment group (test group or placebo group). However, when the treatment information is critical to the subject safety and/or dose escalation decision, the Principal Investigator could be unblinded.

Considering the drug's half-life after administration and study schedule in the single and multiple ascending dose study, safety and tolerability is evaluated within the last pharmacokinetic sampling day of all subjects in the dose group. If it is judged acceptable through the internal SRC review, proceed to the next dose level after discussion and the investigator's judgment has priority for adverse events occurring within the period.

After evaluating the severity of adverse events(safety test results(including clinical laboratory tests, vital signs, etc.) and adverse reactions of all subjects who administered the investigational drug) based on the Common

Terminology Criteria for Adverse Events (CTCAE) version 5.0 or the latest version, the Principal Investigator can decide whether or not to discontinue the entire study. In addition, if the following occurs, the dose escalation can be stopped through discussion between the investigator and the sponsor.

- When a Grade 3 or higher adverse drug reaction occurs in more than 1/4 of the subjects
- When a Grade 4 or higher adverse drug reaction occurs in one or more subjects

During this clinical study period, the administered dose of the investigational drug may be changed based on the results of the previous dose group. And in this case, it will proceed after obtaining approval from the Ministry of Food and Drug Safety to amend the clinical study protocol.

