## 9. Study Subjects

### 9.1. Planned Subject Number and Rationale for sample size determination

This study is a phase 1 study to evaluate the safety, tolerability and pharmacokinetics of KDS2010 and to explore pharmacodynamics of KDS2010 after a single and multiple oral administration of KDS2010. Therefore, it is desirable to proceed with the minimum number of subjects within the limit that satisfies the purpose of the study, so this study is planned with a target number of up to 88 subjects, 8 in each cohort (including placebo).

If, according to the 9.3. Withdrawal Criteria, a subject drops out, and a replacement subject occurs according to the 9.4. Replacement of Study Subjects, the number of subjects may increase. (However, except for cases that only PSV visits are not conducted)

- **Single ascending dose study (including food effect study): Total 48 subjects**

| Cohort | Dosing groups | Dosage        |                           | Number of subjects |
|--------|---------------|---------------|---------------------------|--------------------|
| 1      | 30 mg         | Test group    | KDS2010 30 mg × 1         | 6                  |
|        |               | Control group | KDS2010 30 mg placebo × 1 | 2                  |
| 2      | 60 mg         | Test group    | KDS2010 30 mg × 2         | 6                  |

|                |                      |               |                            |   |
|----------------|----------------------|---------------|----------------------------|---|
|                |                      | Control group | KDS2010 30 mg placebo × 2  | 2 |
| 3 † | 120 mg (food effect) | Test group    | KDS2010 30 mg × 4          | 6 |
|                |                      | Control group | KDS2010 30 mg placebo × 4  | 2 |
| 4              | 240 mg               | Test group    | KDS2010 240 mg × 1         | 6 |
|                |                      | Control group | KDS2010 240 mg placebo × 1 | 2 |
| 5              | 480 mg               | Test group    | KDS2010 240 mg × 2         | 6 |
|                |                      | Control group | KDS2010 240 mg placebo × 2 | 2 |
| 6              | 960 mg               | Test group    | KDS2010 240 mg × 4         | 6 |
|                |                      | Control group | KDS2010 240 mg placebo × 4 | 2 |

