#### **9.4. Replacement of Study Subjects**

In this clinical study, a small number of candidate subjects can be registered in advance in consideration of the dropout rate prior to the first administration, and when dropout occurs before the first administration, the candidate subject can be replaced with the formal subject.

As this clinical study is conducted for exploratory purposes, not hypothesis testing, there is no need to replace subjects even if they drop out. In order to maintain the ratio of subjects receiving the test drug to subjects receiving placebo by dose group, additional subjects may be registered to replace subjects who dropped out. However, in the case of a subject who dropped out due to an adverse event that occurred after administration of the investigational drug, the subject is not replaced.

In the case of replacing a subject who dropped out due to reasons other than adverse events (eg, withdrawal of consent, etc.), replaced subjects are selected in the order that they passed the screening test, and the subject number that has already been used cannot be used. In the case of subject replacement, the subject number of the subject to be replaced shall be marked so that it can be recognized that it is the replaced subject, including the last digit of the number of the subject who dropped out.

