## 10.6. Dose Escalation Stopping Criteria

After evaluating the severity of adverse events(safety test results(including clinical laboratory tests, vital signs, etc.) and adverse reactions of all subjects who administered the investigational drug) based on the Common Terminology Criteria for Adverse Events (CTCAE) version 5.0 or the latest version, the Principal Investigator can decide whether or not to discontinue the entire study. If two or more subjects in a dose group have a dose limiting toxicity defined as a Grade 3 or more than one subject in a dose group have a dose-limiting toxicity defined as a Grade 4 AE related to the investigational drug, the dose escalation may be stopped through discussion.

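### One related Grade 4 reaction is a trigger for stopping escalation in section 10.5, but 10.6 and the synopsis ask for more than one subject

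*Protocol*

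**What the plan says.** Three places in the current protocol text say when escalation may be stopped.

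- **Section 10.5** states that "the dose escalation can be stopped through discussion between the investigator and the sponsor" and gives two conditions. The Grade 3 condition is "When a Grade 3 or higher adverse drug reaction occurs in more than 1/4 of the subjects". The Grade 4 condition is "When a Grade 4 or higher adverse drug reaction occurs in one or more subjects".
- **Section 10.6** states that "the dose escalation may be stopped through discussion" in either of two situations. For Grade 3: "If two or more subjects in a dose group have a dose limiting toxicity defined as a Grade 3". For Grade 4: "more than one subject in a dose group have a dose-limiting toxicity defined as a Grade 4 AE related to the investigational drug".
- **The synopsis**, under its entry on dose escalation stopping criteria, repeats the 10.6 sentence. It does not carry the two conditions from 10.5.

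Section 13.1.2 defines an adverse drug reaction as an event whose causal link to the drug cannot be ruled out. The Grade 4 conditions in 10.5 and 10.6 therefore both count related events. No clause gives one section priority over the other.

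**The concern.** The same action, a discussion about stopping escalation, is tied to two different counts of the same kind of event. In the protocol's own grading scale (section 13.4.1), Grade 4 means life-threatening consequences. After a single such event judged related, a reader of 10.5 would say that a listed stopping condition has been met. A reader of 10.6 or the synopsis would say that it has not. The section and the synopsis entry that are actually titled as stopping criteria both carry the laxer count, and someone working from the synopsis alone would never see the one-subject condition.

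The rule has real work to do in this trial. Section 5.2.1 gives a rat human-equivalent dose of 4.84 mg/kg at the no-adverse-effect level, and 4.84 × 60 kg = 290 mg. The planned 480 mg and 960 mg doses lie above that figure. Section 5.2.1 defends the top dose by a single-dose rat tolerability figure instead.

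**Working it through.** The protocol states no operating characteristic for its stopping rule, so there is no figure of its own to reproduce. Cohort size is consistent: (6 single-dose + 5 multiple-dose cohorts) × 8 = 88, with 6 active and 2 placebo subjects in each (section 9.1).

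**Step 1. Rules side by side.**

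| | Section 10.5 | Section 10.6 and synopsis |
|---|---|---|
| Grade 4 count | 1 subject | 2 subjects |
| Grades named in that limb | 4 or higher | 4 |
| Grade 3 count | more than 1/4, denominator not stated | 2 subjects in a dose group |
| Consequence | can be stopped, after discussion | may be stopped, after discussion |

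**Step 2. Grade 4 limb.** Let x be the number of subjects in a dose group with a related Grade 4 event, with no Grade 3 events.

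- x = 0: neither rule is met.
- x = 1: 10.5 is met (1 ≥ 1); 10.6 and the synopsis are not (1 < 2).
- x = 2: all are met.

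The disagreement at x = 1 stands even if the Grade 3 limb of 10.6 is read generously as Grade 3 or higher, because one subject is still fewer than two. If one further subject has a related Grade 3 event, the outcome depends on that reading. On the literal text 10.6 is still not met (one at Grade 3, one at Grade 4). On the generous reading two subjects meet it.

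**Step 3. Ordering within 10.6.** Grade 3 needs two subjects. Grade 4, read literally, needs more than one, which is also two. The Grade 4 limb is then no stricter than the Grade 3 limb.

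**Step 4. Size, as illustration only.** The protocol gives no event rates, so the rate p of a related Grade 4 event per active subject is an assumption. With 6 active subjects:

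- at least one: 1 − (1 − p)^6
- at least two: 1 − (1 − p)^6 − 6p(1 − p)^5

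At p = 5%: 1 − 0.95^6 = 0.265, and 0.265 − 6 × 0.05 × 0.95^5 = 0.265 − 0.232 = 0.033.

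| Assumed p | One or more (10.5) | More than one (10.6, synopsis) |
|---|---|---|
| 1% | 5.9% | 0.1% |
| 2% | 11.4% | 0.6% |
| 5% | 26.5% | 3.3% |
| 10% | 46.9% | 11.4% |

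If all 8 subjects are counted at the same rate, the pair is 33.7% against 5.7% at 5%, and 57.0% against 18.7% at 10%.

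**Step 5. Grade 3 limb.** Take two subjects with related Grade 3 reactions and nothing higher.

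- Denominator 8 (all dosed): 2/8 is exactly 1/4, not more, so 10.5 needs 3 while 10.6 needs 2.
- Denominator 6 (active only): 2/6 exceeds 1/4, so both are met.

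The protocol does not say which denominator applies. Section 9.4 adds that "there is no need to replace subjects even if they drop out", while also allowing replacements, so the number in a cohort need not stay at 8.

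**The case against.** The strongest reply is that the two sections do not collide in operation. Both are permissive, and neither says that escalation continues below its count. Taken together they can be read as a union, so that one related Grade 4 reaction satisfies 10.5 and nothing in 10.6 cancels it. The safety review committee must in any case find safety and tolerability adequately shown before each next dose level, so such an event would be reviewed whichever count is used. The principal investigator can also discontinue the study under either section, and under section 11.1 can suspend it urgently without consulting the sponsor. Finally, *more than one* is probably a slip for *one or more*. The document is loose with *more than* elsewhere: the meal specification is worded differently in the synopsis and in section 10.4.1, and section 14.1 describes the safety population as those dosed more than once.

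Most of this stands, and it limits the consequence. It does not remove the defect. Nothing in the protocol says that the sections are cumulative, and if 10.5 governed, the Grade 4 limb of 10.6 would be redundant. General powers to stop do not settle whether a stated trigger has been met. A probable slip in a safety threshold still needs correcting, and it appears in both places headed as stopping criteria.

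**Conclusion.** The point holds as an internal inconsistency in a safety trigger. The Grade 4 threshold is one subject in 10.5 and two in 10.6 and the synopsis. The certain case of disagreement is one related Grade 4 event with no Grade 3 event. This rests on the protocol's own definition of an adverse drug reaction and needs no event rates; the percentages in the working depend on assumed rates. It should be fixed, but it is not a threat to the trial's validity.

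Three stronger readings might be inferred, and the documents do not support them.

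- *That the sections force opposite decisions, or that 10.6 forbids stopping after one Grade 4 event.* Both only permit stopping, and committee review comes first at every level.
- *That a related death could pass without action because 10.6 names only Grade 4.* Section 10.5 says Grade 4 or higher, and the committee and investigator powers apply regardless.
- *That the Grade 3 limbs can be mapped exactly, with disagreement only at certain cohort sizes.* The denominator is unstated, 10.5 includes higher grades where 10.6 literally does not, and it is unclear whether the relatedness condition in 10.6 reaches its Grade 3 limb. What can be said is that three of eight dosed subjects are needed under 10.5 against two under 10.6, while two of six on active drug meet both.

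**What to change.** In section 10.6 and the synopsis, replace the Grade 4 condition with: *one or more subjects in a dose group with a related AE of Grade 4 or higher*. This matches 10.5 and restores a stricter count for Grade 4 than for Grade 3.

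For Grade 3, the sponsor and the safety review committee should choose one rule and use it in 10.5, 10.6 and the synopsis. An example is two or more subjects in a dose group with a related AE of Grade 3 or higher. A plain count avoids the unstated denominator, but the choice of count is theirs. If they keep a fraction, they should state whether it is of all dosed subjects or of those on active drug.

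The cost is protocol amendment text in three places, with no change to procedures or sample size. The downside is that the stopping trigger will be met somewhat more often than under the present 10.6 wording.

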## 10.6. Dose Escalation Stopping Criteria

After evaluating the severity of adverse events(safety test results(including clinical laboratory tests, vital signs, etc.) and adverse reactions of all subjects who administered the investigational drug) based on the Common Terminology Criteria for Adverse Events (CTCAE) version 5.0 or the latest version, the Principal Investigator can decide whether or not to discontinue the entire study. If two or more subjects in a dose group have a dose limiting toxicity defined as a Grade 3 or more than one subject in a dose group have a dose-limiting toxicity defined as a Grade 4 AE related to the investigational drug, the dose escalation may be stopped through discussion.

## 10.7. Observations & Assessments

### 10.7.1. Screening test

The screening tests to review the eligibility of the subjects who voluntarily provided a written consent to participate in the clinical study will be performed within 4 weeks from the first administration, and subjects who have clinically significant abnormalities in the following tests will be excluded. Prior to the screening visit, perform the test after fasting for at least 8 hours. (However, if the screening test results are clinically significant, retesting can be carried out up to two times at the discretion of the investigator.)

In order to smoothly conduct clinical study, some subjects may participate as candidate subjects. Candidate subjects will be hospitalized on the same day as the formal subjects assigned with randomization numbers, and if there is a vacancy in the formal subject while participating as a candidate subject (e.g., no show of a formal subject or withdrawal of consent, etc.), the candidate subject may participate in the clinical study as a substitute for a formal subject. If there is no vacancy and the treatment group is terminated, the candidate subject may participate as a formal subject in the other treatment group with the next available schedule.

- 1) Explanation of consent form and obtaining written consent
- 2) Inclusion and exclusion criteria evaluation
- 3) Investigation of demographic data and measurement of height and weight
  - ① At the time of screening, demographic information such as gender and age of the test subject is checked, and drinking and smoking history are asked.
  - ② Measurement of height and weight
    - Height: To 1 decimal place, cm
    - Weight: Rounded from 2 decimal places to 1 decimal place, kg
    - Body mass index: Rounded from 2 decimal places to 1 decimal place, kg/m^2
- 4) Investigation of drug administration history and medical history

Investigate recent medical history, including past medical history within 3 years, and drug administration

history within 5 weeks.

5) Physical examination

Physical examination includes examination of general condition, nutritional status, skin/mucous membranes, eyes (except for visual loss), otolaryngology, thyroid, lung/respiratory system, heart/circulatory system, abdomen, kidney/urogenital system, nerve/psychiatric system, spine/limb/tumors, peripheral circulation, lymphatic system, and other organs.

6) Vital signs

Vital signs include systolic blood pressure, diastolic blood pressure, pulse rate, and body temperature (tympanic membrane). Blood pressure and pulse rate are measured after maintaining a seated position for more than 3 minutes without sudden changes in position.

7) 12-Lead ECG

In addition to the basic recording, the ventricular rate (beats/min), PR interval (msec), QRS (msec), QT/QTcB (msec) at which automatic analysis & recording is output are recorded.

8) Pregnancy test

For all women of childbearing potential except surgical infertility, urine hCG test is performed.

9) Clinical laboratory test

Clinical laboratory tests include the following lists.

|                             |                                                                                                                                                                                                                                                    |
|-----------------------------|----------------------------------------------------------------------------------------------------------------------------------------------------------------------------------------------------------------------------------------------------|
| Hematology test      | WBC with differential count (segmented neutrophil, eosinophil, basophil, lymphocyte, monocyte), RBC, hemoglobin, hematocrit, platelet                                                                                                              |
| Blood chemistry test | AST, ALT, ALP, $\gamma$ -GTP, LDH, CPK, glucose, total cholesterol, triglyceride, creatinine, BUN, uric acid, total bilirubin, total protein, albumin, sodium, potassium, calcium, chloride, phosphorus, eGFR (measured using the CKD-EPI formula) |
| Coagulation test     | PT (INR), aPTT                                                                                                                                                                                                                                     |
| Urine test           | dipstick (color, pH, specific gravity, albumin, bilirubin, glucose, urobilinogen, ketone, nitrite, occult blood, WBC) microscopy (RBC, WBC, squamous cell, others)                                                                                 |

10) Alcohol breathing test

11) Cotinine & Urine drug screening

Amphetamines, barbiturates, benzodiazepines, cannabinoids, cocaine, opiates, cotinine

12) Serology test

HBsAg, HCV-Ab, HIV-Ag/Ab, RPR

13) Neurological examination

A full neurological examination (Appendix 1) is performed.

14) Concomitant medication monitoring

15) Education on precautions for subjects

